## Abstract

**Background:**

Neurological disorders account for a large and increasing proportion of the global burden of disease. Therefore, it is important to strengthen the management of neurologic care, particularly in rural areas. The use of tele-neurology in primary care in rural areas is internationally considered to have the potential to increase access to health care services and improve the quality of care in these underserved areas. NeTKoH aims to address the existing knowledge gap regarding the effects of a tele-neurologic intervention in primary care under real-world conditions in a rural area in Germany.

**Methods:**

NeTKoH is a cluster-randomized controlled trial with a stepped-wedge design involving 33 outpatient general practitioner’s (GP) offices (clusters) in a rural area in Northeast Germany. During 11 predetermined steps, all clusters are randomized before they cross over into groups from the control to the intervention arm. The targeted sample size is 1,089 patients with neurologic symptoms that are continuously being recruited. In the intervention arm, tele-neurologic consultations will be provided via a face-to-face video conferencing system with a neurologic expert at a university hospital. The control arm will receive usual care. The primary outcome is the proportion of neurologic problems being solved at the GP’s office. Secondary outcomes will comprise hospital stays and days, time until neurologic specialist appointments and diagnostics, patients’ health status and quality of life, outpatient and inpatient referrals.

A concurrent observational study, together with a process, implementation, and health economic evaluation, will also be conducted.

**Discussion:**

Using a stepped-wedge cluster design in a real-life situation can help with logistic challenges and enhance the motivation of the participating GPs, as all, at some point, will be in the intervention phase. With the additional implementation evaluation pertaining to external validity, an observational study, and a health economic evaluation, NeTKoH will be able to provide an extensive evaluation for health policy decision-makers regarding the uptake into standard care.

**Trial registration:**

German Clinical Trials Register (DRKS00024492). Date registered: September 28, 2021. Date and protocol version: June 2023, version 1.

**Supplementary Information:**

The online version contains supplementary material available at 10.1186/s12913-023-09724-w.

## Introduction

### Background and rationale

Neurological disorders account for a large and increasing proportion of the global burden of disease [1–3]. In Europe and also in Germany, almost 60% of the general population is affected by a neurological disorder [4]. Many neurologic disorders increase with age [2]. With respect to a progressively aging society in Germany, an increase in neurological diseases is expected [4].

Therefore, it is important to strengthen the management of care to avoid a lack of healthcare services for the population, particularly in rural areas [5]. West Pomerania in the state of Mecklenburg-West Pomerania in Northeast Germany is an area where outpatient care is foremost based on primary care due to the comparatively low density of specialist care available in the region. The increased need for regional specialist care and, thus, neurological expertise confronts local outpatient general practitioners’ (GP) offices, as well as neurologic specialists, with major challenges.

The use of telemedicine or telehealth is widely considered to have the potential to increase access to healthcare services and improve the quality of care in rural and underserved areas, where care with specialized services close to home is not guaranteed [6, 7].

Telemedicine is defined as “the use of electronic and telecommunication technologies to provide healthcare at a distance” [8]. It can take place in real-time via a video conferencing system and has been used for chronic disease management in integrated care [9].

Over the past 25 years, telemedicine has also been applied in neurology (tele-neurology), including clinical neurosciences and acute neurological care [10–12]. In primary care, neurologic telemedicine programs have also been set up using face-to-face video conferencing or teleconsultations. They indicate an improvement in the quality of care in rural areas, patients’ and primary care physicians’ satisfaction, as well as being associated with cost-savings [13–15].

Unlike acute neurological care, the use of tele-neurology in a primary care setting in an underserved rural area in Germany has, to our knowledge, not yet been established and evaluated. This study aims to close this knowledge gap.

### Objectives

The objective of neurologic teleconsultations in GP practices (NeTKoH) is to improve the quality of health care services in an underserved area in Germany through the use of tele-neurology in primary care. Patients with neurological symptoms and diseases in a rural community can receive neurologic specialty care close to home in their familiar GP practice via a face-to-face video conferencing system between the local outpatient GP and a neurologist from a neurology department of a university hospital in the region.

In addition, GPs are offered continued education in aspects of neurology by the neurology department of the participating university hospital. The teleconsultations between GPs and remote neurologists, as well as the continued education, are intended to strengthen on-site care and facilitate the regional care of patients. Furthermore, this interdisciplinary, integrated care approach is aimed at improving in a cost-effective way the coordination of health care management.

With a stepped-wedge cluster randomized controlled trial under real-world conditions, we aim to evaluate the effectiveness of tele-neurologic consultations in primary care on the healthcare system level (proportion of neurologic problems being solved in the GPs` offices, hospital stays, and days), on patients (time until neurologic specialist appointments and diagnostics, health status, quality of life), and health care providers (referrals). For the evaluation of NeTKoH, a stepped-wedge cluster randomized controlled design was chosen to facilitate the roll-out of the intervention and prevent the disappointment of local GPs not randomized to the intervention, as this intervention follows a piloting phase in the region regarding the feasibility of tele-neurology in primary care [16].

In addition, a process, implementation, and health economic evaluation together with a concurrent observational study regarding the effects of continued neurologic education will also be undertaken in connection with this project. This protocol will focus on the trial part of NeTKoH.

## Methods/Design

The study protocol of NeTKoH adheres to the reporting guidelines defined by the SPIRIT 2013 [17] statement (see Supplemental file 1), the TIDieR checklist [18], CONSORT [19] and its extension for stepped-wedge cluster randomized trials (SW-CRT) [20].

### Design

NeTKoH is a cluster randomized controlled trial following a cross-sectional stepped-wedge design with continuous recruitment and a short exposure period*.*

During NeTKoH, the tele-neurologic intervention will be rolled out sequentially to 33 GP offices (clusters) from the control to the intervention arm. The control arm will receive care as usual. The overall trial period of 36 months and 17 days is divided into 11 "steps" with a length of 12 weeks each. Individual steps are extended by 1—2 weeks to account for school vacation periods.

In the 1st step of this pragmatic trial, all clusters start in the control phase. At each subsequent step, 3 to 4 randomly selected clusters will switch to the intervention phase. At the beginning of the 11th step, all clusters will have entered the intervention phase (see Fig. 1). This design was chosen under the given time limits by the funding agency to take the impact of COVID-19 on primary care settings in fall 2021 into account. The originally planned design consisted of 12 steps, with 3 randomly selected clusters switching at each step. A cluster was defined as a GP practice established according to the German health care planning requirements.

**Fig. 1 Fig1:**
[figure not shown]
Schematic illustration of roll-out and timeline of the NeTKoH trial

### Study setting, eligibility criteria, and recruitment

The study is conducted in an outpatient primary care setting in rural West Pomerania in the state of Mecklenburg West Pomerania in Northeast Germany. Eligible study sites had to be (1) located in the region of West Pomerania, (2) managed by GPs or internists, (3) who see patients with statutory health insurance, and (4) have the technical and spatial requirements for establishing teleconsultations.

GPs in the region were contacted by an informational letter about the project via the local Association of Statutory Health Insurance Physicians and the regional university hospital University Medicine Greifswald (UMG). Informational meetings regarding the intervention were held 10 months before the start of the trial. After expressing written consent, interested GPs were visited by the project planners of the NeTKoH group. The study design was explained, and further instructions, including a handout, were given. A cooperation agreement was then signed with 33 GPs. All participating GPs were granted a monetary incentive of 100 € per included patient to foster their cooperation. A list of study sites can be obtained from the NeTKoH study group.

### Participants, eligibility criteria, and recruitment

Patients admitted to NeTKoH have to be (1) at least 18 years old, (2) present themselves with neurological symptoms (any symptoms that can warrant a referral to a specialist in neurology) to the participating GP, (3) members of a statutory health insurance, and (4) able to give informed consent.

Due to the variance and broadness of neurological symptoms, the review of an extensive symptom list by the GP during the patient appointments was deemed not realistic by experts involved in the project. In addition, symptom categories always represent a simplification that does not do justice to the complexity of neurological diseases. Moreover, the project does not focus on a specific neurological disease. Therefore, due to medical, pragmatic, and methodological reasons, the "presence of a neurological deficit according to the assessment of the GP" or the question of the GP "Would you like to have a neurological teleconsultation?" was considered as a more appropriate way to screen potential participants.

Patients are excluded if the GP considers them to have a neurological emergency (e.g., stroke) that requires prompt inpatient attention or if they are unable to give informed consent. Patients can only be admitted once with the same neurological problem to the trial.

Given the open cohort design, patients are continuously screened and recruited by the GPs when they present with a neurologic symptom.

### Intervention

During the intervention phase of the trial, all clusters will receive neurologic teleconsulting. In order to do so, they will be equipped with a certified telemedical system (VIMED® Praxis) provided by the company MEYTEC (Werneuchen, Germany). This telemedicine device is a face-to-face video-conferencing tool connected with the department of neurology at UMG. It allows for a remote audiovisual interaction between a tele-neurologist located at UMG and the participating GP, together with the patient. The NeTKoH video-conferencing system is a hardware solution with integrated microphones and speakers, as well as a remotely controllable camera. Internet access is achieved via mobile radio.

Eligible patients can be included in the study by the participating GPs after informed consent is given by the patients in the course of their consultation visit. Patients, who are willing to participate in the study, will be asked to wait while a medical assistant of the GP’s office activates the telemedical system in a separate room in order to start the registration process for the consultation electronically. Through the registration, a medical assistant located at the neurology department (UMG), is notified and schedules an appointment. Thereby, a notification appears on the telemedicine device located in the GPs office. The GP’s office will then schedule the consultation and will inform the patient about the planned start of the consultation with the tele-neurologist, which then takes place in the GP’s examination room. The teleconsultation, which is supposed to be limited to a maximum of 15 min, includes questions about symptoms, diagnostics performed, treatments, referrals, medications, and a brief symptom-oriented clinical examination. After the consultation, the findings and recommendations are electronically documented and a print-out in the GP’s office is created.

During the time a cluster is randomized to the control phase, treatment will be provided according to ‘usual care’ after informed consent is given by the patient. This means that clusters delivering the control condition will not be equipped with a telemedicine device, and patients will have no access to a tele-neurologist during their GP visit. Treatment will follow local standards.

### Outcomes

Outcomes pertain to the health care system (macro level), the institution (meso level) as well as the individual (micro level).

The primary outcome is the proportion of neurologic problems being solved in the GPs’ practices, measured by the number of patients without an outpatient referral (neurologic/other specialists), inpatient referrals (hospital), or other.

The secondary outcomes include on the macro level: (1) number of hospital stays, (2) length of hospital stay, on the meso level (3) number and types of referrals, and on the micro level (4) time until neurologic appointments, (5) time until specialty diagnostics, (6) quality of life, and (7) health status.

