### Participant timeline

The data for the primary outcome will be measured after the GP appointment (*t*_*1*_^*GP*^) with a self-complete paper survey (control arm) and collected in the NeTKoH database by the tele-neurologist (intervention arm) at *t*^*T*^. At baseline (*t*_*0*_^*GP*^), organizational and demographic data of the settings and GPs will be collected with a survey by the study center.

Secondary outcome data (see Table 1) regarding the enrolled patient’s quality of life and health status will be assessed for both groups after the GP appointment regarding a neurologic problem (*t*_*0*_^*P*^) with the self-complete EQ-5D-5L. In order to minimize interference in the GP offices’ everyday routine, only this time point (*t*_*0*_^*P*^) was deemed feasible. Patients’ demographics will also be collected in a self-complete paper survey. Their disease characteristics will be documented by the GPs at *t*_*1*_^*GP*^ in the GP survey. The subsequent treatment (referrals) of patients and further process-related data will be documented by the tele-neurologist in the NeTKoH-database at *t*^*T*^. Just-in-time care endpoints, such as time until a neurologist appointment, and specialty diagnostics, as well as the number of hospital stays, will be assessed at *t*_*1*_^*P*^ for both groups taken in the form of a standardized telephone interview 3 months after the patients’ initial GP appointment. All patient answers to the standardized questions at the 3-month follow-up (*t*_*1*_^*P*^) will be electronically documented by the study team. The patients’ length of stay (LOS) at the hospital between *t*_*0*_^*P*^ and *t*_*1*_^*P*^ will be collected via claims data provided by the two participating health insurance providers.

**Table 1 Tab1:** NeTKoH—secondary outcomes, timepoints^a^, and instruments

Outcome	Timepoint	Measurement instrument
Subsequent treatment (referrals): GP/neurologist/other medical specialist/inpatient care/others *(intervention group – control group)*	*t*_*1*_^*GP*^*, t*^*T*^	Questionnaires GPs, NeTKoH-database
Time until appointment neurologist (days) *(intervention group – control group)*	*t*^*T*^ *t*_*1*_^*P*^	*Intervention group*: NeTKoH-database *Control group*: standardized phone interview

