### Statistical methods: sample size and power calculations.

The study includes 33 clusters in the region of West Pomerania, in which the participating university hospital is located. Sample size calculations were based on the Hussey & Hughes approach [22] for stepped-wedge cluster design for analysis with fixed time effects and random cluster effects.

The sample size calculation was based on the primary endpoint. As a basis for this calculation, we took the assumption that in the control group, the proportion of outpatient neurological symptoms that can be solved in the GP's practice (i.e., there is no subsequent neurological or special outpatient consultation or inpatient referral) is 0.2 (20%). We expect a 50% improvement (i.e., a 50% increase in effect size on the risk difference scale) in the intervention group, corresponding to an expected proportion of 0.3 (30%) in the intervention group.

With a total sample size of 1,089 participants (corresponding to 555 patients included in the control phase and 534 patients included in the intervention phase) at a type I error rate of 0.05, and an assumed coefficient of variation of 0.25, the study has a power of 80%, at a coefficient of variation of 0.20 and a power of 81% to measure the assumed effect size or a larger effect. Due to the nature of the intervention and the immediate collection of the primary endpoint data following the intervention, no attrition pertaining to this endpoint can be expected.

To achieve this number of cases, the stepped-wedge cluster randomized trial (CRT) must recruit, on average, at least 3 patients meeting the inclusion criteria, per cluster and step, to perform an appropriate analysis for this design.

To examine secondary endpoints (except those using claims data), all patients included during the study can be analyzed. Based on an estimate from experts of the NeTKoH study group, we assume an average demand of 6 to 8 neurological consultations per GP per month, which means about 3,168 neurological consultations per year in the whole region. Of these, about 25% of patients* (N = 792 per year, N = 66 per month) are insured by the participating statutory health insurances AOK Nordost and Techniker Krankenkasse. Assuming a loss of 30% due to non-participation or loss-to-follow-up, complete data of about 554 neurological consultations of the AOK Nordost and Techniker Krankenkasse patients per year and of about 1,269 to 1,690 patients during the whole study period are possible.

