### Statistical analysis

The principal analysis focuses on the effect of the tele-neurological intervention, defined by the primary outcome, namely the proportion of neurologic problems being solved in the GPs’ practices, to answer the following question: *Do neurological teleconsultations in GP practices lead to an increase in the proportion of patients with neurological issues resolved in the GP practice in comparison to care as usual?*

A generalized linear mixed effects model will be used, in accordance with the sample size and power considerations above, to adjust for time-specific confounding and intra-cluster correlations. We assume time and intervention effects are common to all clusters, and model them as fixed effects. The random cluster effects allow accounting for intra-cluster correlation. Related sensitivity analyses will be described in the Statistical Analysis Plan.

We will report point estimates of the intervention effect along with 95% confidence intervals on absolute and relative scales (respectively measured as rate difference and rate ratio). Estimated correlations and time coefficients will also be reported.

The secondary analyses will assess the secondary outcomes and consist of testing the different study assumptions also using generalized linear mixed effects models (for secondary outcomes 1, 2, 4, 5, 6, 7), as well as a cluster-adjusted chi-squared test (for secondary outcome 3). For all analyses, we consider a significance level of 0.05.

The statistical analyses will be performed using R v4.2.2 (or higher, [24]). A comprehensive, detailed Statistical Analysis Plan, with details on handling missing values and ancillary analyses at individual and cluster levels, will be prepared before data locking and extraction for the statistical analysis.

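### Secondary outcome 3 (referrals) is defined in two ways, and its chi-squared test gives no effect estimate and, as named, no adjustment for calendar time

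*Protocol article*

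**What the plan says.** Three places in the protocol article fix this outcome.

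- **Outcomes** names it as item "3) number and types of referrals", at the institutional level.
- **Participant timeline, Table 1** describes it as "Subsequent treatment (referrals): GP/neurologist/other medical specialist/inpatient care/others", taken from the GP questionnaires and the trial database.
- **Statistical analysis** gives it a "cluster-adjusted chi-squared test (for secondary outcome 3"). The other six secondary outcomes get generalized linear mixed models. The section adds: "For all analyses, we consider a significance level of 0.05".

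The primary outcome is the proportion of problems solved in the practice, "measured by the number of patients without an outpatient referral (neurologic/other specialists), inpatient referrals (hospital), or other".

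**The concern.** The text describes a count and a kind. The table describes one classification, and its last four levels match the routes whose absence defines success on the primary outcome. The natural reading of the remaining level, GP, is that the patient stays with the GP, which is that success. The article does not say so; this is an inference.

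Three things are at stake.

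1. The Objectives section presents referrals as the provider-level result, apart from the system-level primary outcome. A single p-value could be reported there without showing whether fewer patients were referred, the types shifted, or the primary effect reappeared.
2. A chi-squared test compares category frequencies. It gives no effect size with an interval, and it does not analyse how many referrals each patient had.
3. The test as named allows for clusters only. In a stepped wedge the share of intervention patients rises with every step, so any drift in referral habits is mixed into an unadjusted comparison. The article gives time adjustment as a reason for its mixed model, yet this one outcome is left without it.

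**Working it through.** **Inputs from the article.** 33 clusters; 11 steps; sequences of 4, 3, 3, 3, 3, 3, 3, 3, 4, 4 clusters; 3 patients per cluster and step; 555 control and 534 intervention patients; solved in the practice 0.20 versus 0.30; alpha 0.05, taken as two-sided. Design effects and referral mixes are assumptions, since the article gives neither for this test.

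**1. The plan's own figures.** Sequence k spends k steps in control, so the control cells number 4×1 + 3×(2+…+8) + 4×9 + 4×10 = 185 and the intervention cells 363 − 185 = 178. Times 3 this is 555 and 534, as stated.

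The Hussey & Hughes variance is Iσ²(σ² + Tτ²) / [(IU − W)σ² + (U² + ITU − TW − IV)τ²]. Here I = 33, T = 11, U = 178, W = 3,990, V = 1,260, σ² = 0.25×0.75/3 = 0.0625 and τ = 0.25×0.20 = 0.05.

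- Numerator: 33×0.0625×0.09 = 0.1856.
- Denominator: 1,884×0.0625 + 10,828×0.0025 = 144.82.
- Standard error: √(0.1856/144.82) = 0.0358.
- Power: Φ(0.1/0.0358 − 1.96) = 79.8%, against a stated 80%. With a coefficient of variation of 0.20 it is 81.6%, against a stated 81%.

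The schedule and rates are therefore read correctly.

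**2. Five-level test when only the GP share changes.** Let the referral types keep the same mix in both conditions. Each type then falls by the same factor (0.7/0.8), so the type cells together contribute what a single any-referral cell would. The noncentrality therefore does not depend on the mix:

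λ = (n₁n₂/N)(p₂ − p₁)² / [p̄(1 − p̄)]

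- p̄ = (555×0.20 + 534×0.30)/1,089 = 271.2/1,089 = 0.2490
- n₁n₂/N = 555×534/1,089 = 272.15
- λ = 272.15×0.01/(0.2490×0.7510) = 14.55

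Rejection probability of a noncentral chi-squared with 4 degrees of freedom and noncentrality λ divided by the design effect:

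| Assumed design effect | λ | Rejection |
|---|---|---|
| 1 | 14.55 | 88% |
| 1.3 | 11.19 | 77% |
| 1.5 | 9.70 | 70% |
| 2 | 7.28 | 56% |

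For comparison, GP versus any referral as a two-level test has the same λ on 1 degree of freedom and rejects in 97% at design effect 1. A test of the four types among referred patients only (about 444 and 374) rejects at the nominal 5%.

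**3. Calendar time.** The control step numbers sum to 4×1 + 3×(3+6+10+15+21+28+36) + 4×45 + 4×55 = 761, so the mean control step is 761/185 = 4.1. All steps sum to 33×66 = 2,178, so the mean intervention step is (2,178 − 761)/178 = 8.0. The gap is 3.85 steps. The article gives no trend. As an assumption, a linear drift of 0.5, 1 or 2 percentage points per step in a referral proportion would give an unadjusted difference of 1.9, 3.9 or 7.7 points with no intervention effect.

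**4. Does analysing each type separately remove the overlap?** No. With 60% of referred patients going to a neurologist, that proportion among all patients moves from 0.8×0.6 = 48% to 0.7×0.6 = 42%. Then z = 0.06/0.0302 = 1.99, and the test rejects in about 51% without clustering. With a 40% share (32% versus 28%), z = 1.44 and it rejects in about 30%.

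**The case against.** A reader might infer that outcome 3 simply tests the primary outcome again, and that it would report a change in referrals where there was none. The article supports neither.

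- It never defines the GP level as no referral, and it does not say that all five levels enter one test. Table 1 may only list recorded options, and the category set can properly be left to the statistical analysis plan. This stands, so the rejection figures are conditional.
- The outcome covers number as well as type. If referred patients fall from 80% to 70%, referrals have changed and a rejection is correct. It misleads only if read as a change in type. The 5% comparison answers a different question, in a subgroup formed after allocation. This also stands.
- A 4-degree-of-freedom test overlaps the primary contrast but is not the same test (88% against 97%), and overlap between a primary outcome and its breakdown is common. This stands.
- Number may mean the number of patients per referral type, which a chi-squared test can compare. The article nowhere says that one patient contributes several entries, so a breach of independence is hypothetical. This stands. The meaning of number still has to be stated.
- Hospital use is covered in part elsewhere: stays and length of stay are separate outcomes with mixed models. Inpatient referrals are not the same thing, so this only softens the point.

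None of this answers the rest. The two definitions differ in the article itself, and the test is named there for this outcome alone, without time adjustment or an effect estimate.

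**Conclusion.** The point holds as a minor one. The text and Table 1 define outcome 3 differently, and the test chosen fits a stepped wedge less well than the model the article uses for every other secondary outcome.

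The 88%, 70% and 56% rest on five assumptions: GP means no referral, all five levels are tested together, each patient has one level, the planned 20% versus 30% is true, and the type mix is unchanged. The design effects of 1.5 and 2 are also assumed. Under these conditions a rejection is a true finding about referrals, but no evidence of a shift in type and no confirmation independent of the primary outcome.

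The gap of almost four steps needs none of these assumptions; it follows from the planned schedule with equal recruitment per cluster and step. How much it matters depends on a secular trend that the article does not quantify, though its Discussion names such trends as a limitation.

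The primary analysis, the sample size and the data collected are unaffected.

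**What to change.** 1. Use one definition of outcome 3 in the Outcomes section and in Table 1. Say what the GP level means, whether patients without a referral are included, and what number counts.
2. Replace the chi-squared test with the mixed model used for the other secondary outcomes: fixed time and intervention effects and a random cluster effect. Fit it to the number of referrals per enrolled patient and to each type (neurologist, other specialist, inpatient, other) as yes/no in all enrolled patients. Report each estimate with a 95% confidence interval. If the forms record only one destination per patient, the number is 0 or 1 and the complement of the primary outcome; in that case report the types only.
3. State that both the total and the type-specific results depend on the primary outcome (working, step 4).

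The cost is a wording change and a few more model fits on data already planned, settled in the statistical analysis plan before data lock. The downside is several estimates, with their multiplicity, in place of one p-value: four type-specific tests at 0.05 allow a family-wise error of up to 4×0.05 = 20%. The emphasis should therefore be on the intervals.
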